- h Pregnancy test for women of childbearing potential only. For male subjects with female partners of childbearing potential, pregnancy tests are strongly recommended. Male subjects whose partners are pregnant must be instructed to use a condom to minimize exposure of RBV to the partner. Female subjects of childbearing potential and their male partners must use 2 effective contraceptive methods during treatment and for 4 months after all treatment has ended. Male subjects and their female partners of childbearing potential must use 2 effective contraceptive methods during treatment and for 7 months after all treatment has ended.
- i Serum ( $\beta$ -HCG) pregnancy test at screening and serum or urine pregnancy test before first dose of treatment to ensure that women are not pregnant at the time of starting treatment.
- j For female subjects of childbearing potential, pregnancy testing (serum or urine) should occur monthly during telaprevir combination therapy and for 4 months after all treatment has ended. For male subjects with female partners of childbearing potential, pregnancy testing should occur monthly during telaprevir combination therapy and for 7 months after RBV therapy has ended.
- k If not performed in the past or subject to change at screening.
- l At screening a complete physical examination should be performed. At all other visits up to 30 days after the last dose of telaprevir, physical examinations should be directed at detecting adverse events. All physical examinations performed more than 30 days after the last dose of telaprevir should be completed according to clinical practice.
- m Electrolyte disturbances (eg, hypokalemia, hypomagnesemia, and hypocalcemia) should be monitored and corrected, if necessary, before initiation and during telaprevir therapy.
- n A posttreatment HCV RNA level that is measured at a time point at least 12 weeks after the last dose of treatment may be reported if HCV RNA is not measured at 24 weeks after the last dose of treatment.
- o Drug accountability only for telaprevir.
- p Collect all concomitant therapies for rash and anemia, regardless of adverse event severity grade, and all concomitant therapies for serious adverse events through 30 days after last dose of telaprevir.

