##### **4.1. Inclusion Criteria**

Each potential subject must satisfy all of the following criteria to be enrolled in the early access program. Each subject must:

1. Be a man or woman, between 18 and 70 years of age, inclusive
2. Have evidence of HCV infection genotype 1 (molecular assay)
3. Have a quantifiable plasma HCV RNA
4. Have documentation of liver fibrosis assessed by liver biopsy or non-invasive test (eg, fibrotest, fibroscan) showing severe fibrosis (Metavir F3 or Ishak 3-4) or cirrhosis (Metavir F4 or Ishak 5-6). For subjects with Metavir F3 or Ishak 3-4, the liver biopsy or non-invasive test should have been performed within the past 18 months.
5. Have compensated liver disease (Child-Pugh Grade A clinical classification) (see Attachment 1)
6. Have access to the Hepatitis C standard-of-care (Peg-IFN-alfa/RBV)

7. If a women of childbearing potential, must have a negative serum  $\beta$ -human chorionic gonadotropin ( $\beta$ -hCG) pregnancy test documented at the screening visit and a negative serum or urine pregnancy test before the first dose of study drug to ensure that they are not pregnant at the time of starting treatment.
8. If heterosexually active, a female subject of childbearing potential and a nonvasectomized male subject who has a female partner of childbearing potential must agree to use 2 effective contraceptives from screening onwards until 4 months (female subject) or 7 months (male subject) after all therapy has ended.

Note: Hormonal contraceptives may not be reliable during telaprevir dosing. Therefore, to be eligible for this early access program, subjects should use 2 other effective birth control methods during telaprevir combination therapy and for 2 months after the last intake of telaprevir (see also Section 4.3).

9. Sign the informed consent document indicating that they understand the purpose of and procedures required for the early access program and are willing to participate in the early access program.

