#### **4.3. Prohibitions and Restrictions**

Refer to Section 8, Prestudy and Concomitant Therapy for contraindications to telaprevir. Because telaprevir must be used in combination with RBV and Peg-IFN, the contraindications and warnings applicable to those medicinal products are applicable to combination therapy. For contraindications and warnings to Peg-IFN-alfa and RBV, please refer to the relevant local prescribing information of these products.

The prohibitions and restrictions required for participation in this early access program were based on the following:

- Telaprevir has shown no teratogenic potential in rats and mice and is not considered a developmental toxicant in these species. Significant teratogenic and/or embryocidal effects have been demonstrated in all animal species exposed to RBV. Extreme care must be taken to avoid pregnancy in female subjects (see Prohibitions and Restrictions Criteria 1, 2, and 3) and in female partners of male subjects (see Prohibitions and Restrictions Criteria 1 and 4; also refer to the local prescribing information for RBV).
- In female subjects, the co-administration of telaprevir with an estrogen-based hormonal contraceptive reduced ethinylestradiol exposure (see Prohibitions and Restrictions Criterion 5).
- It is not known whether telaprevir is excreted in human breast milk. When administered to lactating rats, levels of telaprevir and its major metabolite were higher in milk compared to those observed in plasma. Rat offspring exposed to telaprevir in utero showed normal body weight at birth. However, when fed via milk from telaprevir-treated dams, body weight gain of rat pups was lower than normal (likely due to taste aversion). After weaning, rat pup body weight gain returned to normal. (See Prohibitions and Restrictions Criterion 6; local prescribing information for RBV.)
- Telaprevir had no effects on fertility or fecundity when evaluated in rats.

Potential subjects must be willing and able to adhere to the prohibitions and restrictions described in this section during the course of the early access program to be eligible for participation.

1. As any birth control method can fail, at least 2 reliable forms of effective contraception must be used.
2. Female subjects of childbearing potential and their male partners must use 2 effective contraceptive methods during treatment and for 4 months after all treatment has ended

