3. For female subjects of childbearing potential, pregnancy testing (serum or urine) should occur monthly during telaprevir combination therapy and for 4 months after all treatment has ended
4. Male subjects and their female partners of childbearing potential must use 2 effective contraceptive methods during treatment and for 7 months after all treatment has ended. Male subjects whose partners are pregnant must be instructed to use a condom to minimize exposure of RBV to the partner. Pregnancy testing in non-pregnant female partners is recommended before telaprevir combination therapy, every month during telaprevir combination therapy, and for 7 months after RBV therapy has ended.
5. Estrogen-based hormonal contraceptives may not be reliable during telaprevir dosing. Therefore, female subjects of childbearing potential should use 2 additional methods of effective birth control during telaprevir dosing and for 2 months after the last intake of telaprevir. Examples of non-hormonal methods of contraception include a male condom with spermicidal jelly OR female condom with spermicidal jelly (a combination of a male condom and a female condom is not suitable), a diaphragm with spermicidal jelly, or a cervical cap with spermicidal jelly. As of 2 months after completion of telaprevir treatment, estrogen-based hormonal contraceptives can again be used as 1 of the 2 required effective methods of birth control; however, specific local prescribing information recommendations should be respected.
6. Because of the potential for adverse reactions in breast-fed infants, breast-feeding must be discontinued prior to initiation of therapy.

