If a subject discontinues treatment before the end of the treatment phase, obtain early treatment discontinuation and follow-up assessments, unless informed consent for further follow-up has been withdrawn.

For all subjects, it is recommended that a posttreatment follow-up visit (including sampling for HCV RNA) be performed 24 weeks after the last administered dose of treatment (ie, telaprevir, Peg-IFN-alfa, or RBV) (eg, Week 48 for subjects receiving

24 weeks of treatment, Week 72 for subjects requiring 48 weeks of treatment, 24 weeks after last administered dose of treatment for subjects who discontinue treatment early or withdraw from the open-label treatment phase without withdrawing informed consent).

Subjects who discontinue study drugs prematurely will be instructed to continue the contraception and pregnancy testing procedures outlined in Section 4.3, Prohibitions and Restrictions until 4 months (female subjects of childbearing potential) or 7 months (male subjects and their female partners of childbearing potential) after the last intake of RBV, depending on the local prescribing information.

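### For early stoppers, Section 10.2 counts contraception and female pregnancy testing from the last ribavirin dose, while Sections 4.1 and 4.3 and footnotes h and j count from the end of all treatment

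*Protocol*

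**What the plan says.** Section 10.2, in the text after the table of discontinuation reasons, addresses subjects who stop study drugs prematurely. It tells them to go on with the Section 4.3 contraception and pregnancy-testing procedures. For male subjects the period is "7 months (male subjects and their female partners of childbearing potential) after the last intake of RBV, depending on the local prescribing information"; for female subjects of childbearing potential it is 4 months from the same point.

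The places that set those procedures use a different starting point:

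- Contraception, both sexes. Section 4.1 criterion 8 makes agreement to it a condition of entry, "until 4 months (female subject) or 7 months (male subject) after all therapy has ended".
- Contraception, female subjects. Under Section 4.3 item 2 and footnote h, they and their partners "must use 2 effective contraceptive methods during treatment and for 4 months after all treatment has ended".
- Contraception, male subjects. Under Section 4.3 item 4 and footnote h, they and their partners "must use 2 effective contraceptive methods during treatment and for 7 months after all treatment has ended".
- Testing, female subjects. Section 4.3 item 3 and footnote j say that "pregnancy testing (serum or urine) should occur monthly during telaprevir combination therapy and for 4 months after all treatment has ended".
- Testing, partners of male subjects. Section 4.3 item 4 recommends it before therapy, then "every month during telaprevir combination therapy, and for 7 months after RBV therapy has ended". Footnote j uses the same ribavirin anchor.

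**The concern.** Section 10.2 refers to Section 4.3 for the procedures and then gives an end date that Section 4.3 does not contain. This is hard to put down to loose wording. The paragraph just before it in Section 10.2 counts the follow-up visit from the last dose of any of the three drugs, and Section 4.3 item 4 separates the two anchors within one item. The protocol thus distinguishes the end of all treatment from the end of ribavirin.

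At stake is a subject instruction. Two sites could give the same subject different end dates, depending on which section they open. Under Section 10.2 a subject could stop contraception while still on treatment, contrary to what she agreed to at entry. No text says which section prevails. The closing clause about local prescribing information does not say whether it lengthens or shortens the period.

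**Working it through.** The plan states no figure here, so the check compares the texts and then the dates.

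**1. The rules side by side**

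| Rule | Section 10.2 counts from | Elsewhere counts from | Conflict |
|---|---|---|---|
| Contraception, female, 4 months | last ribavirin | end of all treatment (4.1 criterion 8, 4.3 item 2, footnote h) | yes |
| Contraception, male and partner, 7 months | last ribavirin | end of all treatment (4.1 criterion 8, 4.3 item 4, footnote h) | yes |
| Testing, female, 4 months | last ribavirin | end of all treatment (4.3 item 3, footnote j) | yes |
| Testing, partner, 7 months | last ribavirin | end of ribavirin (4.3 item 4, footnote j) | no |

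**2. When the dates differ.** Let T, R and P be the weeks of the last telaprevir, ribavirin and peginterferon doses, and m the 4 or 7 months.

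- Section 10.2 end = R + m
- Section 4.3 end = max(T, R, P) + m
- Gap = max(T, R, P) − R

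Section 6 allows telaprevir only together with both other drugs, and Section 9.3.1.2 stops it when ribavirin is permanently stopped for anemia. Telaprevir therefore should not outlast ribavirin, and the gap reduces to max(0, P − R). It is zero when ribavirin is last or stops with the last drug. The Section 10.2 date is never the later one.

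**3. Whether P can exceed R.** It can.

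- Anemia (Section 9.3.1.2 and the Section 10.2 table): permanent ribavirin discontinuation requires telaprevir to stop. Nothing requires peginterferon to stop.
- Rash (Sections 9.3.1.1.3.1 and 9.3.1.1.3.2 and the Section 10.2 table): ribavirin may be interrupted with peginterferon continued, and restart depends on improvement within 14 days.
- The note under the Section 10.2 table ties discontinuation of each of these two drugs to its own label. Only ribavirin monotherapy is ruled out.

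**4. Size.** One month = 365.25 / 12 / 7 = 4.348 weeks, so 4 months = 17.4 weeks and 7 months = 30.4 weeks. Assumed case: ribavirin and telaprevir stop at Week 8 for anemia. Section 10.2 then ends at 8 + 17.4 = Week 25.4 (female) and 8 + 30.4 = Week 38.4 (male).

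| Peginterferon ends | Section 4.3 end, female | Section 4.3 end, male contraception | Gap |
|---|---|---|---|
| Week 8 | 25.4 | 38.4 | 0 weeks |
| Week 24 | 41.4 | 54.4 | 16 weeks |
| Week 48 | 65.4 | 78.4 | 40 weeks |

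With peginterferon to Week 48, a ribavirin stop at Week 4 gives 48 − 4 = 44 weeks, and a stop at Week 20 gives 48 − 20 = 28 weeks.

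**5. Whether Section 10.2 can end before treatment does.** It does so when the gap exceeds 17.4 weeks (female) or 30.4 weeks (male). In the Week 8/Week 48 case it ends 48 − 25.4 = 22.6 weeks (female) and 48 − 38.4 = 9.6 weeks (male) before the last peginterferon dose. In the Week 8/Week 24 case it does not.

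**The case against.** **The named hazard is covered.** Section 4.3 attributes teratogenicity to ribavirin and reports none for telaprevir in rats and mice. Section 10.2 keeps the full 4 or 7 months after ribavirin. This stands. A reader might infer that subjects are left unprotected against the known teratogen, and the protocol does not support that. The earlier date means fewer weeks of contraception, not a named hazard left uncovered.

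**Both rules can be obeyed.** Because the Section 10.2 date is never later, a site that follows Section 4.3 also satisfies Section 10.2. This is true, and it makes the conflict milder. It does not help a site that reads Section 10.2 alone, and that is the section written for early stoppers.

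**The trigger is unclear.** The Definition of Terms and Section 9.1.3 use study drug for telaprevir, while Section 9.3.1.1.3.1 uses the plural for all three drugs. The Week 8 anemia case fits the telaprevir reading, since telaprevir stops early. It fits the all-three reading only if peginterferon also stops before its planned end, as at Week 24 of a planned 48. A ribavirin stop at Week 12, with telaprevir complete and peginterferon running to its planned Week 48, would fit only if stopping any one drug counts. It is therefore not used here.

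**The large gaps are near-extremes.** The duration rules treat peginterferon and ribavirin as a pair, and nothing prescribes long peginterferon treatment alone. This stands. A reader might take about 40 weeks as typical, but it is the limit of one assumed case.

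**Conclusion.** The inconsistency is real and limited to contraception in both sexes and testing of female subjects. Partner testing agrees in all places. It has an effect only when ribavirin stops for good before peginterferon. The gap then equals the remaining peginterferon weeks, and the Section 10.2 date is the earlier one.

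The stop weeks above are assumptions. The protocol gives neither the number of such subjects nor how long they would stay on peginterferon alone; they are probably few. No analysis changes: Section 12.3.3 ends pregnancy reporting 30 days after the last telaprevir dose, and Section 11.5 summarizes adverse events over the same window. This is a minor point of subject protection that should be corrected.

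A reader might also conclude that Section 10.2 should require unbroken monthly testing once ribavirin stops. That goes beyond Section 4.3. If item 3 is read as monthly testing only while telaprevir is taken, such a rule would test women who are off ribavirin more often than women still taking it after Week 12.

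**What to change.** Change one sentence in Section 10.2, and the matching subject instruction:

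- for contraception and for testing of female subjects, replace the last ribavirin intake with the end of all treatment as the starting point, keeping 4 and 7 months;
- for testing of male subjects' partners, keep 7 months after the end of ribavirin;
- reword the closing clause so that the period is longer if the local prescribing information requires it, and never shorter.

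Using the ribavirin anchor everywhere would also remove the conflict, but it would mean rewriting an entry criterion, three items of Section 4.3 and two footnotes, and would shorten the present rule.

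Separately, if the phrase telaprevir combination therapy is thought unclear, define it in Section 4.3 item 3 and footnote j for all subjects. The note to Section 4.1 criterion 8 says that "subjects should use 2 other effective birth control methods during telaprevir combination therapy and for 2 months after the last intake of telaprevir", while Section 4.3 item 5 words the corresponding rule as "should use 2 additional methods of effective birth control during telaprevir dosing and for 2 months after the last intake of telaprevir". The phrase may therefore mean telaprevir dosing only, or the whole regimen.

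The cost falls only on subjects whose ribavirin stops first: extra weeks of contraception equal to the gap, and a later end to female testing. There is no cost when all drugs stop together.

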### **10.3. Withdrawal From the Study**

A subject will be withdrawn from the early access program for any of the following reasons:

- Lost to follow-up
- Withdrawal of consent
- The investigator considers, for efficacy or safety reasons, it is in the best interest of the subject
- Death

If a subject withdraws from the early access program before the end of the treatment phase, obtain early treatment discontinuation/early withdrawal and follow-up assessments, unless informed consent for further follow-up has been withdrawn.

If a subject is lost to follow-up, every reasonable effort must be made by the study site personnel to contact the subject and determine the reason for discontinuation/withdrawal. The measures taken to follow up must be documented in the source documents.

When a subject withdraws before completing the early access program, the reason for withdrawal is to be documented in the CRF and in the source document. Study drug assigned to the withdrawn subject may not be assigned to another subject.

## **11. STATISTICAL METHODS**

### **11.1. Analysis Population**

The intent-to-treat analysis population will be defined as all enrolled subjects who received at least 1 dose of telaprevir. The intent-to-treat analysis population will be used for all statistical analyses, unless otherwise specified.

### **11.2. Subject Information**

Descriptive statistics will be provided for all subjects who receive at least 1 dose of telaprevir.

### 11.3. Efficacy Analyses

There are no efficacy assessments and as such no formal planned efficacy analyses in this early access program. The HCV RNA data will be summarized using descriptive statistics (n, percent).

### 11.4. Sample Size Determination

No formal sample size calculation has been performed. The trial is not designed to evaluate a specific statistical hypothesis but to provide subjects with early access to telaprevir. Therefore, the number of enrolled subjects is not based on statistical but rather practical considerations involving the expected prevalence of HCV infection in the included countries and the projected number of eligible subjects based on major eligibility criteria along with other available therapies. Nonetheless, safety and tolerability data will be summarized using descriptive statistics. The percentage of subjects having selected safety and tolerability events will be estimated and 95% confidence intervals (CIs) for these estimates will be derived. Although no formal statistical hypotheses regarding overall response rates will be tested, the following table provides some guidance on the precision of estimation as measured by the half-width of the derived 95% CIs. For example, if the expected percentage of subjects with a serious adverse event is 10%, the expected 95% confidence interval would be approximately (8.9%, 11.1%) with 3,000 subjects.

| Expected Half-Width of 95% Confidence Intervals for Percentage of Subjects With an Event |                           |              |              |
|-------------------------------------------------------------------------------------------------|---------------------------|--------------|--------------|
| Estimated Event Rate (%)                                                                 | Number of Subjects |              |              |
|                                                                                                 | 2,000              | 3,000 | 4,000 |
| 10                                                                                       | 1.3                       | 1.1          | 0.9          |
| 20                                                                                       | 1.8                       | 1.4          | 1.2          |
| 30                                                                                       | 2.0                       | 1.6          | 1.4          |
| 40                                                                                       | 2.1                       | 1.8          | 1.5          |
| 50                                                                                       | 2.2                       | 1.8          | 1.5          |

### 11.5. Safety Analyses

Safety analyses will be performed for descriptive purposes only. There will be no inferential statistical analyses. Although there is no control arm and statistical comparisons are not formally planned, multiple logistic regression and subgroup analyses may be used to assess the variability of selected safety parameters across potential prognostic factors including, but not limited to, demographic, treatment, and other baseline characteristics. These will be viewed as hypothesis-generating rather than hypothesis testing analyses. These methods will be described in the Statistical Analysis Plan which will be finalized prior to database lock.

There are no planned interim analyses of safety data. However, the safety data may be used for standard safety reporting required for health authority submissions or requests.

